Access to healthcare is often reduced in rural compared to urban communities. For example, Huron County in rural southwestern Ontario has a 27.5% physician vacancy rate (number of positions available for general practitioners) compared to 0% vacancy rate in nearby urban centres [20]. Innovative technologies including mobile health monitoring have the potential to increase access to healthcare. Our group completed a pilot study testing the feasibility and utility of deploying a mobile health technology kit for self-management of metabolic syndrome risk factors and physical activity in a rural population [21,22]. Twenty-four participants aged 30-72 years monitored their blood pressure three times per week and blood glucose two times per day with Bluetooth™ enabled devices paired with a smartphone. Additionally, pedometer steps were manually inputted daily and body weight was inputted weekly [21,22]. A health monitoring system including an application on the smartphone and a secure online database was used to transmit and store data [21]. Alarms were triggered when measurements were outside of pre-determined limits. Following the eight-week intervention, waist circumference, diastolic blood pressure and total cholesterol were reduced, physical activity and fitness were increased [22], and autonomic function was improved [23]. Furthermore, participants reported that the technology assisted in adopting new practices to improve wellbeing and did not take too much time or interfere with activities of daily living [21]. This study, however, could not conclude whether the mobile health protocol had added benefit to the exercise prescription.

Therefore, the purpose of this trial was to investigate the effects of a mobile health supported exercise prescription, compared to exercise prescription alone on metabolic syndrome and other global cardiometabolic risk factors in individuals at risk for cardiovascular disease and type 2 diabetes. It was hypothesized that the primary outcome, systolic blood pressure, and secondary outcomes would be improved in both groups, but to a greater extent in the mobile health intervention group at 12 weeks and that these changes would be better maintained at 24 and 52 weeks in the intervention group with mobile health support compared with the active control group.

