## Methods/Design

### Study design

This study was a randomized controlled trial with two intervention arms: 1) the intervention group, which received a tailored exercise prescription and a mobile health technology kit; and 2) the active control group, which received only a tailored exercise prescription. Adults aged 18-70 years were screened for inclusion. Participants (*n* = 149) presenting with at least two metabolic syndrome risk factors reported to the clinic (Gateway Rural Health Research Centre, Seaforth, Ontario, Canada) at baseline (V0) and for 12- (V1), 24- (V2) and 52-week (V3) follow-up visits.

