#### *Sample size calculation*

The sample size was based on differences in mean change between the intervention and active control groups in systolic blood pressure (primary outcome measure) at 12-weeks. The sample size calculation assumed 80% power and two-sided significance level of 0.05. We estimated that the smallest difference between groups in mean change that would be expected was 6 mmHg and we assumed a common standard deviation of 12 mmHg. Therefore, it was determined that 63 participants would be required per group. By assuming a 15% drop-out rate, this would increase our required sample size to 73 participants per group. Since we are using an Analysis of Covariance (ANCOVA) to perform data analysis (primary analysis), this sample size estimation may be considered conservative.

Data will be analysed following the Intent-to-Treat approach. Analyses will include all safety evaluable patients who have both baseline and valid post-baseline data. In instances where a participant may not have completed the final visit of the protocol but was subjected to the above procedures before study termination, a last observation carried forward approach will be used for analysis. Baseline data will not be carried forward.

For all continuous outcome variables, distributions will be examined to assess normality and presence of outliers; transformations will be undertaken as appropriate. For categorical outcome variables, frequency tables will be examined to ensure there are no out-of-range values.

Descriptive statistics will be computed for baseline demographic characteristics and for all outcome measures, at each time point. Specifically, means and standard deviations will be calculated for continuous variables and frequency counts and percentages will be calculated for categorical variables.

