#### *52-week analyses*

The 12-week analyses will be extended to include data collected at all time-points. Linear mixed models will be used for continuous outcomes. Within these models, the group variable will indicate differences between groups at baseline, the time variable will indicate change over time in the reference (i.e., active control) group, and the group × time variable will indicate whether change over time differs between groups. Contrast statements will be used to determine change over time in the intervention group.

A similar approach will be followed for categorical variables; however, generalized linear (logistic) mixed models will be used instead. Interpretation of study results will be primarily based on estimation and associated 95% confidence intervals [40]. Analyses will be performed using R 3.0.1 [41].

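### Last observation carried forward is unnecessary beside the planned mixed models, overstates within-arm maintenance after dropout, and can bias the 52-week comparison in either direction

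*Protocol article*

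**What the plan says.** The missing-data rule stands under Sample size calculation in the protocol article. Its trigger is "In instances where a participant may not have completed the final visit of the protocol"; for such participants "a last observation carried forward approach will be used for analysis". The same paragraph adds "Baseline data will not be carried forward" and defines the analysis set: "Analyses will include all safety evaluable patients who have both baseline and valid post-baseline data". The rule names no outcome, time point or model.

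Study design sets the assessments "at baseline (V0) and for 12- (V1), 24- (V2) and 52-week (V3) follow-up visits".

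Under 52-week analyses the plan reads: "The 12-week analyses will be extended to include data collected at all time-points. Linear mixed models will be used for continuous outcomes". Logistic mixed models are planned for categorical outcomes. That section does not say whether carried-forward values enter these models.

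The Background hypothesises a larger improvement with mobile health support at 12 weeks and "that these changes would be better maintained at 24 and 52 weeks in the intervention group with mobile health support". The Discussion repeats this for systolic blood pressure.

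**The concern.** The only values that can be carried are week 12 (to weeks 24 and 52) and week 24 (to week 52). Those later visits exist to show whether an early improvement lasts. For someone who leaves after week 12, the rule sets the change from week 12 to week 52 to exactly zero. The protocol's own Discussion makes that hard to believe, since it reports that long-term benefit of lifestyle programmes depended strongly on continuing the behaviours.

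The rule is also not needed. A mixed model fitted by likelihood uses every observed visit of a participant who later drops out, and is valid under missing at random. Entering copied values replaces that assumption with a stronger one and treats the copies as measurements. At stake are the 24- and 52-week estimates and their 95% confidence intervals, on which the article says interpretation will mainly rest.

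**Working it through.** **The plan's own figures.** Inputs from Sample size calculation: difference 6 mmHg, SD 12 mmHg, two-sided 0.05, power 80%.

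- n per group = 2 × (1.960 + 0.842)² × 12² / 6² = 62.8, rounded up to 63, as stated.
- 63 × 1.15 = 72.45, rounded up to 73, as stated.

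Both rest on the 12-week contrast. The rule cannot fill week 12, so neither figure changes.

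**Within-arm maintenance.** Let d be the share who leave after week 12 and q the fraction of the week-12 change that they truly keep. The rule credits them with 1, so retention in that arm is overstated by d × (1 − q).

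- d = 15%, q = 0: 15 percentage points.
- d = 15%, q = 0.5: 7.5 points.
- d = 30%, q = 0: 30 points.

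**Between-arm contrast at week 52.** From the plan: SD 12 and 15% dropout. Assumed, because the documents give no figure: 75 per group (149 / 2 ≈ 75), correlation 0.5 between visits, relapse of 6 mmHg with half of it by week 24, half of dropouts leaving after week 12 and half after week 24, and dropouts following their own arm's course.

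A dropout after week 12 has 6 mmHg of relapse hidden; one after week 24 has 3 mmHg hidden. The average is (6 + 3) / 2 = 4.5 mmHg. The bias in intervention minus control is therefore 4.5 × (control dropout, if control relapses) − 4.5 × (intervention dropout, if intervention relapses).

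| Scenario | Dropout, intervention / control | True difference | Carried forward |
|---|---|---|---|
| Only control relapses | 15% / 15% | -6 | -6 + 0.15 × 4.5 = -5.3 |
| Only control relapses | 30% / 30% | -6 | -6 + 0.30 × 4.5 = -4.65 (simulated about -4.6) |
| Both relapse equally | 10% / 25% | 0 | 4.5 × (0.25 − 0.10) = +0.7 |

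Swapping the dropout rates in the last row reverses the sign.

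**Rejection rates.** With correlation 0.5, the SD of a change is 12 × √(2 × 0.5) = 12. Simulated t-tests on change at week 52 gave about 77% with carried values against 80% with observed values at 15% dropout, and about 64% against 72% at 30%.

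**The opposite direction.** Now assume week-12 changes of -12 (intervention) and -6 (control), 15% leaving each arm after week 12, completers keeping half and dropouts keeping none.

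- True: 0.85 × 0.5 = 42.5% retained, so the difference is 0.425 × (-6) = -2.55.
- Carried forward: 0.425 + 0.15 = 57.5% retained, so the difference is 0.575 × (-6) = -3.45.

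Here the rule inflates the difference by 0.9 mmHg. Over all the retention and dropout patterns tried in this second set-up, the bias ran from -1.8 mmHg (favouring the intervention) to +0.9 mmHg (against it).

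**The case against.** A reader might infer that the rule assumes the answer to the maintenance hypothesis. The documents do not support that. The hypothesis is comparative, and the rule freezes dropouts in both arms. In the first two table rows, where the hypothesis is true, carrying forward works against it. What is presupposed is maintenance within an arm, among dropouts.

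It can also be said that the 52-week section may mean collected data only, and that filling week 24 is never spelled out. That reading is possible, but it leaves an unrestricted rule in one section in conflict with the model in another. An edit is needed either way.

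The sizes depend on relapse and dropout patterns that the documents do not give. At the stated 15% dropout the shift in the first scenario is under 1 mmHg and costs about 3 points of power. This stands, and it limits the severity.

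Finally, observed-only analysis is not free of bias if dropouts relapse more than completers. In the last example completers alone give 0.5 × (-6) = -3.00, against a truth of -2.55 and -3.45 with carrying forward, so dropping the rule removes only about half of the error. This also stands. It calls for a sensitivity analysis and does not justify keeping the rule.

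**Conclusion.** The point holds for the 24- and 52-week analyses and is a should-fix. The rule credits every dropout with full maintenance from the last attended visit, which overstates within-arm retention by up to 15 points at 15% dropout if dropouts relapse fully. It can move the 52-week between-arm difference either way. Under the tabulated assumptions the shift is about 0.7 mmHg at 15% dropout in each arm, about 1.4 mmHg at 30%, and about 0.7 mmHg from a true zero with 10% against 25%.

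A reader might take this as a threat to the trial's main result. It is not one: the 12-week ANCOVA of systolic blood pressure and the sample size are untouched. Nor do the documents fix the direction of the bias. Correlation, size and timing of relapse, and any difference in dropout between arms are assumptions; only the 6 mmHg difference, SD 12 and 15% dropout come from the plan.

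**What to change.** Delete the carry-forward sentence, or keep it only as a labelled sensitivity analysis. Under 52-week analyses, state that the linear and logistic mixed models are fitted by likelihood to observed visits only, under missing at random. As a useful optional addition, include one sensitivity analysis that shifts post-dropout values toward baseline, because dropouts may relapse more than completers.

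The cost is a change of text and, if adopted, one extra analysis; no new data are needed. The downside is slightly wider confidence intervals and reliance on missing at random.

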#### *12-week analyses*

For all continuous outcomes, ANCOVA will be used to examine differences in mean change between and within groups, while adjusting for baseline levels of the outcome of interest. For categorical outcomes, binary variables will be derived and we will use logistic regression to model the odds of improvement in either the intervention or active control group, while adjusting for baseline levels of the outcome of interest.

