#### *Recruitment and screening process*

This study was approved by the University of Western Ontario Research Ethics Board (Protocol #15828). Community-dwelling adults aged 18-70 years were recruited via newspaper or radio advertisement, flyers, referral from healthcare professional and word of mouth. Interested candidates contacted the study coordinator for telephone screening. Participants were eligible if they had two or more metabolic syndrome risk factors according to National Cholesterol Education Program Adult Treatment Panel III criteria: waist circumference ≥ 88 cm (women) or ≥ 102 cm (men); systolic blood pressure ≥ 135 mmHg and/or diastolic blood pressure ≥ 85 mmHg; fasting plasma glucose ≥ 6.1 mmol/L; triglycerides ≥ 1.7 mmol/L; and high density lipoprotein cholesterol ≤ 1.29 mmol/L (women) or ≤ 1.02 mmol/L (men) [24]. Exclusion criteria were: systolic blood pressure > 180 mmHg and/or diastolic blood pressure > 110 mmHg; type 1 diabetes; history of myocardial infarction, angioplasty, coronary artery bypass or cerebrovascular ischemia/stroke; symptomatic congestive heart failure; atrial flutter; unstable angina; unstable pulmonary disease; use of medications known to affect heart rate; second or third degree heart block; history of alcoholism, drug abuse or other emotional cognitive or psychiatric problems; pacemaker; unstable metabolic disease and orthopedic or rheumatologic problems that could impair the ability to exercise. Participants who passed the initial screening were booked for a V0 appointment. To facilitate scheduling of group mobile health technology training sessions, block randomization was used, such that all participants attending appointments during week one were allocated to the intervention group and all participants attending appointments during week two were allocated to the control group and so on.

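### Whole appointment weeks were allocated to one arm, but the sample size and the 12-week ANCOVA treat participants as individually allocated, so interval coverage and the stated 80% power are not assured.

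*Protocol article*

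**What the plan says.** **Allocation** (Protocol article, Recruitment and screening process). The reason and the method are given as "To facilitate scheduling of group mobile health technology training sessions, block randomization was used". In practice, "all participants attending appointments during week one were allocated to the intervention group"; those seen the following week went to the other arm, and the weeks continued to alternate. Each appointment week therefore lies wholly within one arm.

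**Sample size** (Sample size calculation). "The sample size calculation assumed 80% power and two-sided significance level of 0.05". The target is stated as "the smallest difference between groups in mean change that would be expected was 6 mmHg", with a common standard deviation of 12 mmHg. This gives 63 per group, raised to 73 for 15% drop-out. No week size, ICC or design effect appears. Because ANCOVA is the primary analysis, the section adds that "this sample size estimation may be considered conservative".

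**12-week analysis** (12-week analyses). "ANCOVA will be used to examine differences in mean change between and within groups". The only adjustment named is the baseline level of the outcome.

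**52-week analysis** (52-week analyses). "Linear mixed models will be used for continuous outcomes". Group, time and their interaction are described; random effects are not. The same section says interpretation rests primarily on estimates with 95% confidence intervals.

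**The concern.** When whole weeks are allocated, the week is the unit of allocation. If outcomes of people enrolled in the same week are correlated, each arm holds less independent information than its head count suggests. Standard errors that ignore this are too small, so intervals are too narrow and the type I error exceeds 5%.

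The text gives some reason to expect a positive correlation. Weeks were used so that the intervention arm could be trained in groups, in a session of about two hours. Follow-up is at fixed intervals, so people enrolled together tend to be re-measured at about the same time.

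Two stated items are affected: the primary 12-week comparison, and the claim that the sample size errs on the safe side. That claim counts the precision gained from baseline adjustment but not the precision that allocation by week may cost.

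**Working it through.** **Inputs from the article:** difference 6 mmHg, SD 12 mmHg, two-sided 0.05, 80% power, 63 analysed per group. The 149 enrolled are consistent with this: 149 × 0.85 / 2 = 63.3.

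**Inputs assumed, because the article does not give them:** week size m, within-week ICC, and baseline-to-follow-up correlation ρ.

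**1. Reproduce the plan's figure.**
n = 2 × (1.960 + 0.842)² × (12/6)² = 62.8, so 63 per group. Power at 63 is Φ(0.5 × √(63/2) − 1.960) = 80.1%. The figure reproduces with independent participants and no design effect.

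**2. Add clustering.**
- Design effect: DE = 1 + (m − 1) × ICC
- Type I error of an analysis that ignores week: 2 × [1 − Φ(1.960/√DE)]
- Width of the unadjusted interval relative to the correct one: 1/√DE
- Power of a correctly sized test: Φ(0.5 × √(63/(2 × DE)) − 1.960)
- Required n per group: 62.8 × DE, rounded up

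| m | ICC | DE | Type I error | Coverage | Relative width | Power at 63 | n per group for 80% |
|---|---|---|---|---|---|---|---|
| any | 0 | 1.00 | 5.0% | 95.0% | 1.00 | 80.1% | 63 |
| 5 | 0.01 | 1.04 | 5.5% | 94.5% | 0.98 | 78.6% | 66 |
| 5 | 0.05 | 1.20 | 7.4% | 92.6% | 0.91 | 72.6% | 76 |
| 10 | 0.05 | 1.45 | 10.4% | 89.6% | 0.83 | 64.4% | 92 |

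**3. Allow for the ANCOVA gain.** Take 12 mmHg as the SD of change, with equal variances at baseline and 12 weeks. ANCOVA then multiplies the variance by (1 + ρ)/2, which is 0.75 at ρ = 0.5 and 0.85 at ρ = 0.7. Power uses DE × (1 + ρ)/2 in place of DE.

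| DE | Power, ρ = 0.5 | Power, ρ = 0.7 |
|---|---|---|
| 1.00 | 90.0% | 86.1% |
| 1.20 | 84.1% | 79.4% |
| 1.45 | 76.8% | 71.5% |

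Power stays at about 80% or more up to DE = 1/0.75 = 1.33 at ρ = 0.5, and up to 1/0.85 = 1.18 at ρ = 0.7. The type I error and coverage in step 2 are unchanged for a given residual ICC, because ANCOVA without a week term still computes its standard error as if participants were independent.

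**4. Few weeks.** A week-level test also loses degrees of freedom. With 10 per week there are about 12 weeks (63/10, about 6 per arm) and 10 degrees of freedom. Power is then 71.6% even at ICC 0, before any ANCOVA gain. With 5 per week (about 13 per arm, 24 degrees of freedom) it is 76.8% at ICC 0.

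**The case against.** The strongest reply is that nothing in the article shows a material within-week correlation.

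- **Size.** At ICC 0 the intervals are correct, and at 5 per week with ICC 0.01 the type I error is only 5.5%. This stands: the loss may be negligible.
- **ANCOVA reserve.** The article cites it, and step 3 shows it can keep power above 80% at moderate design effects. This stands for power, not for coverage.
- **Sources of correlation.** There is one clinic, exercise counselling was individual, and those who missed group training were trained individually. Alternating weeks largely balances slow seasonal drift between arms, and baseline adjustment removes week differences already present at baseline. The relevant ICC is therefore the residual one, which may be small. A reader might infer that staff, equipment or recruitment source were shared within a week and differed between weeks; the article does not say so.
- **One-sided clustering.** Group training exists only in the intervention arm. If only that arm were clustered, the inflation at 5 per week and ICC 0.05 would average (1.20 + 1.00)/2 = 1.10. That gives a type I error of 6.2% and power of 76.3% before ANCOVA: smaller, but in the same direction.
- **Mixed models.** A reader might infer that the 52-week models also ignore week. The article does not support this: it describes no random effects at all, not even for participant, and an analysis plan that is not shown may specify them.

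None of this removes the mismatch between the allocation and the stated sample size and 12-week model.

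**Conclusion.** The point holds for the sample size and the 12-week ANCOVA. Both are written for individually allocated participants, while allocation was by week. If within-week correlation is positive, the error runs one way, towards intervals that are too narrow.

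Over the cases shown, the type I error is 5.5% to 10.4%, and power before ANCOVA gain is 78.6% to 64.4%. These figures rest on assumed week sizes of 5 and 10, ICCs of 0.01 and 0.05, equal clustering in both arms and large-sample formulas.

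It would be tempting to say that the intervals are too narrow and that 80% power is not delivered. The article does not establish either, since both depend on an unreported week size and ICC, and power also depends on the ANCOVA gain. The supportable statement is that coverage, the 80% power and the description as conservative are not assured. For the 52-week models the point is only that the handling of week should be confirmed.

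**What to change.** 1. Account for appointment week in the 12-week ANCOVA. Use either a random intercept for week with Kenward-Roger or Satterthwaite degrees of freedom, or week-clustered standard errors with a small-sample correction.
2. Make sure the 52-week linear and logistic mixed models also account for week, and state their random effects.
3. Report the number and size of weeks by arm, and the estimated ICC.
4. Restate the 80% power as holding under independence, with a range over stated ICCs and week sizes. Qualify the description of the sample size as conservative.

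**Cost.** In modelling terms the change is small: the appointment week determined each participant's arm, so it is known, and the analyses are still described as future work. The statistical price is wider intervals and lower stated power. The amount depends on the number of weeks and the ICC, and it may be more than slight if weeks are few, as step 4 of the working shows.

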## Abstract

**Background:**

Metabolic syndrome is a cluster of cardiovascular risk factors that greatly increase the risk of developing cardiovascular disease and type 2 diabetes. Regular exercise improves the risk profile, but most people do not successfully change their exercise habits to beneficially reduce risk. Tailored exercise prescribed by a family physician has shown promise as a means to increase fitness and reduce cardiometabolic risk, but optimal implementation practices remain unknown. Mobile health technologies have proved to be a beneficial tool to achieve blood pressure and blood glucose control in patients with diabetes. These technologies may address the limited access to health interventions in rural and remote regions. However, the potential as a tool to support exercise-based prevention activities is not well understood. This study was undertaken to investigate the effects of a tailored exercise prescription alone or supported by mobile health technologies to improve metabolic syndrome and related cardiometabolic risk factors in rural community-dwelling adults at risk for cardiovascular disease and type 2 diabetes.

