### Final eligibility screening at baseline visit

Participants who qualified for the study reported to the clinic following an eight hour fast. Participants were instructed to abstain from caffeinated or alcoholic beverages for 12 hours and intense physical activity for 24 hours prior to their study visits. Voluntary informed consent was obtained from all participants. Inclusion and exclusion criteria were verified by a medical history interview and by measuring metabolic syndrome risk factors.

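### Within-arm change is made an inferential target, but with the prescription in both arms and eligibility values reused as baseline it cannot show that the exercise prescription works

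*Protocol article*

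**What the plan says.** All references are to the protocol article.

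- **Analysis at 12 weeks** (12-week analyses): for all continuous outcomes, ANCOVA is to examine "differences in mean change between and within groups", adjusted for the baseline level of the outcome. Descriptive means and SDs at each time point are promised separately under Sample size calculation, so the within-group part is additional output.
- **Analysis at 52 weeks** (52-week analyses): in the mixed model "the time variable will indicate change over time in the reference (i.e., active control) group", and "Contrast statements will be used to determine change over time in the intervention group". Interpretation is to rest mainly on estimates and 95% confidence intervals.
- **Hypothesis** (Background, last paragraph): the primary and secondary outcomes "would be improved in both groups, but to a greater extent in the mobile health intervention group at 12 weeks".
- **Aim** (Abstract, Background): to "investigate the effects of a tailored exercise prescription alone or supported by mobile health technologies".
- **Design** (Study design): both arms receive the tailored prescription; the intervention arm also receives the mobile health kit. No arm goes without a prescription.
- **Baseline** (Final eligibility screening at baseline visit): "Inclusion and exclusion criteria were verified by a medical history interview and by measuring metabolic syndrome risk factors". This takes place at V0, the visit from which change is measured. No separately re-measured baseline is described.
- **Limitations** (Discussion): volunteer motivation and study-provided phones are listed. Regression to the mean and the lack of an untreated arm are not.

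**The concern.** The hypothesis has two limbs. The second, a greater improvement with mobile health support, is a randomised comparison. The first, improvement in both arms, can be examined only through within-arm change, and the analysis sections provide for exactly that.

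The design gives the first limb no reference. A participant who qualifies because a V0 reading lies beyond a cut-off will on average read closer to the population mean at 12 weeks even if nothing is done. Medication changes, which are asked about at each follow-up visit, and the motivation of volunteers, which the Discussion acknowledges, enter within-arm change as well. None of these can be separated from the prescription when every participant receives it.

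At stake is what the trial may conclude. A fall in both arms could be presented as support for exercise prescription as such, a question that this design cannot answer.

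**Working it through.** **1. The plan's own figure.** Inputs from Sample size calculation: difference in mean change 6 mmHg, SD 12 mmHg, 80% power, two-sided 0.05.

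n = 2 × (1.96 + 0.8416)² × 12² / 6² = 62.8, rounded up to 63 per group. Then 63 × 1.15 = 72.45, rounded up to 73. Both stated figures are reproduced. They rest on the between-group difference, so the within-arm tests play no part in them.

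**2. Precision of within-arm change.** Reading 12 mmHg as the SD of change, the standard error is 12/√63 = 1.51 mmHg, and the 95% interval half-width is 1.96 × 1.51 = 2.96 mmHg.

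**3. Regression to the mean if everyone qualified on systolic pressure.** The documents give no source-population distribution or visit-to-visit correlation, so these are assumptions: mean μ 125-135 mmHg, SD s 14-18 mmHg, and correlation ρ set so that the SD of change is 12, that is ρ = 1 − 144/(2s²), or 0.63 to 0.78.

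Expected fall = (1 − ρ) × s × φ(z)/(1 − Φ(z)), with z = (135 − μ)/s. By simulation this is 3.2 to 6.7 mmHg. It does not describe this trial, because raised blood pressure is one of five possible entry factors.

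**4. Regression to the mean under the actual entry rule.** Simulated with no true effect, taking participants with at least two of five factors and each of the other four present with probability p, independently of systolic pressure (assumed):

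| p | Mean fall per arm (mmHg), across μ and s |
|---|---|
| 0.3 | 1.19 to 1.57 |
| 0.5 | 0.44 to 0.63 |
| 0.7 | 0.11 to 0.18 |

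The overall range is about 0.1 to 1.6 mmHg. It is not simply the figure in step 3 times the share qualifying on systolic pressure. With μ = 130, s = 16 and p = 0.3 that product is 4.53 × 0.57 = 2.58 mmHg, but the simulated fall is 1.41 mmHg, because participants who enter with readings below 135 tend to regress upward.

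**5. Consequence for a within-arm test.** The chance of a nominally significant fall in one arm with no true effect is about Φ(δ/1.51 − 1.96), where δ is the artefact:

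- δ = 0: 2.5%
- δ = 1.00: about 10%
- δ = 1.57: Φ(1.04 − 1.96) = Φ(−0.92) = 17.8%

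For independent arms, a false fall in both at δ = 1.57 has probability 0.178² = 3.2%, against 0.025² = 0.06% without the artefact.

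**6. The between-group contrast.** In the scenario μ = 130, s = 16, p = 0.3, with 63 per arm and no true effect, the ANCOVA group difference averaged −0.06 mmHg with type I error 4.9%. In the same trials the within-arm fall averaged 1.4 mmHg and was declared significant in 16%.

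**7. Other outcomes.** Each participant meets at least two of five criteria, so on average a criterion is met by at least 2/5 = 40% of participants, and selection also acts on secondary outcomes. The documents give nothing from which to size it.

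**The case against.** The strongest reply is that the trial is comparative throughout where it matters. The main-text purpose is mobile-health-supported prescription compared with prescription alone. The sample size rests on the between-group difference, and the Discussion restates the systolic pressure hypothesis as a greater reduction with support, without the both-arms limb. Selection at V0 is expected to act equally in both arms and so cancels from that contrast. All of this stands, and it is why the point does not touch the primary result. How allocation by appointment week affects comparability of the arms is a separate matter.

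A reader might infer that the trial would report regression to the mean as an effect of exercise. The documents do not support that: no section says that within-arm change will be attributed to the prescription or sets a success rule for it. The most that follows is that the text leaves this reading open.

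A reader might also set a fall of 3 to 7 mmHg against the planned 6 mmHg. That fails twice. The larger falls apply only to people selected on systolic pressure, and 6 mmHg is a difference between arms, from which a shift common to both drops out.

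Finally, estimating change in each arm with an interval is legitimate and helps in judging whether improvements are maintained at 24 and 52 weeks. That also stands. The difficulty lies in testing within-arm change against zero to support "secondary outcomes would be improved in both groups", not in reporting it.

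**Conclusion.** The point holds in a limited form. The both-arms limb of the hypothesis, and the within-arm inference planned for it at 12 and 52 weeks, ask a question that the design cannot answer. That does not depend on how large regression to the mean is, since medication changes and other time effects are confounded with the prescription in the same way.

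For systolic pressure the artefact is modest: about 0.1 to 1.6 mmHg per arm, and a false fall in one arm in up to about 18% of trials instead of 2.5%. The upper end needs the other risk factors to be fairly uncommon (p = 0.3). At p = 0.7 the excess is negligible. These figures rest on the assumed distribution, on independence of the factors and on 12 mmHg as the SD of change. The planned between-group analysis and the sample size are unaffected.

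**What to change.** - **12-week and 52-week analyses:** present within-arm change as descriptive estimates, without tests or efficacy claims. Treat the control arm's time term and the intervention arm's contrast alike; removing only one would leave the arms reported unevenly.
- **Effect conclusions:** draw them only from the ANCOVA group term and the group × time term.
- **Background hypothesis and Abstract aim:** reword both to the comparison of mobile-health-supported prescription with prescription alone.
- **Discussion, limitations:** state that without an untreated arm the effect of the prescription itself cannot be estimated, and that within-arm change includes regression to the mean because eligibility and baseline share the V0 values.

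The sample size stays at 63 per group, 73 with dropout. The cost is wording, plus giving up the claim that both programmes improve outcomes. As recruitment is described in the past tense, the change to the hypothesis should be dated and declared as a clarification.
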